## Abstract

**Background:**

There is only limited evidence available on how best to prevent childhood obesity and community-based interventions hold promise, as several successful interventions have now been published. The Victorian Government has recently funded six disadvantaged communities across Victoria, Australia for three years to promote healthy eating and physical activity for children, families, and adults in a community-based participatory manner. Five of these intervention communities are situated in Primary Care Partnerships and are the subject of this paper. The interventions will comprise a mixture of capacity-building, environmental, and whole-of-community approaches with targeted and population-level interventions. The specific intervention activities will be determined locally within each community through stakeholder and community consultation. Implementation of the interventions will occur through funded positions in primary care and local government. This paper describes the design of the evaluation of the five primary care partnership-based initiatives in the *'Go for your life' Health Promoting Communities: Being Active Eating Well *(HPC:BAEW) initiative.

**Methods/Design:**

A mixed method and multi-level evaluation of the HPC:BAEW initiative will capture process, impact and outcome data and involve both local and state-wide evaluators. There will be a combined analysis across the five community intervention projects with outcomes compared to a comparison group using a cross-sectional, quasi-experimental design. The evaluation will capture process, weight status, socio-demographic, obesity-related behavioral and environmental data in intervention and comparison areas. This will be achieved using document analysis, paper-based questionnaires, interviews and direct measures of weight, height and waist circumference from participants (children, adolescents and adults).

**Discussion:**

This study will add significant evidence on how to prevent obesity at a population level in disadvantaged and ethnically diverse communities. The outcomes will have direct influence on policy and practice and guide the development and implementation of future obesity prevention efforts in Australia and internationally.

**Trial registration:**

ACTRN12609000892213

## Background

Obesity is a growing public health issue and there is now widespread agreement that the complex etiology of obesity requires a multifaceted approach to prevention [1-4]. Community-based interventions provide an opportunity for community assets to be utilized with efficiency and direction [3]. There is now emerging evidence of the effectiveness of community-based and community-wide, multi-strategy approaches to obesity prevention [1,5-9].

A community-based, capacity-building approach aims to promote sustainable skill development, strengthen communities and increase the ability of individuals to effectively address and improve health outcomes [10,11]. Such an approach has the potential to influence the underlying social and economic determinants of health in a flexible, sustainable, equitable and safe manner [12]. To determine the sustainability of effective intervention activities, evaluation is required both in the intermediate and long term [13].

The aim of this paper is to describe the evaluation design of the five Primary Care Partnership (PCP)-based intervention sites in the *Health Promoting Communities: Being Active Eating Well *(HPC:BAEW) initiative to promote healthy eating and physical activity in disadvantaged communities across Victoria, Australia. The intervention will operate at a whole-of-community level within five intervention sites using a multi-setting, multi-strategy capacity-building approach. The evaluation objectives are to: 1) assess the extent to which the initiatives have been implemented as planned (process evaluation), and 2) evaluate the impacts and outcomes of the intervention when compared to a comparison sample.

## Methods/Design

### Intervention communities

Each intervention community has a specific primary target population, which ranges from children aged 0-12 years (including primary/elementary school students); to adolescents aged 12-18 years (secondary school students) and working adults. Secondary target populations include the wider community, older adults and specific disadvantaged groups (e.g. low income, ethnic minority, rural) within the community. The primary and secondary target groups for each intervention community are shown in Table 1, along with the characteristics of the communities.

**Table 1 T1:** Intervention community characteristics and target groups.

Intervention Community	Community characteristics	Primary target group	Secondary target group
**1**	Rural and urban townships High percentage of socio-economic disadvantage	Primary school aged children	Families, carers, older adults and seniors
**2**	Urban Culturally and linguistically diverse Socio-economic disadvantage	Children 0-12 years	Families, carers, older adults and seniors
**3**	Rural townships High percentage of socio-economic disadvantage Significant proportion of young people	Secondary school aged children	Older adults
**4**	Urban Culturally and linguistically diverse High percentage of socio-economic disadvantage	Secondary school aged children	Young people newly arrived from overseas
**5**	Rural Culturally homogenous Ageing population group High percentage of socio-economic disadvantage	Working adults	Wider community

### Preparation for evaluation

The evaluation was not funded until after the funding and initiation of the five intervention projects. Therefore, prior to developing the evaluation plan, draft project action plans were reviewed in detail in conjunction with the project coordinators and affiliates for each of the projects and a matrix was developed to provide an overview of the implementation activities in each community. This is presented in Table 2.

**Table 2 T2:** The intervention approaches for the objectives of the five Health Promoting Communities: Being Active Eating Well intervention communities*.

	Intervention approach				
Intervention objectives	Capacity building	Policy development & implementation	Community strengthening	Health skills & action competencies	Social marketing
Increase consumption of healthy food at home and/or in the community	2,4	4	2	2,4,5	2
Increase consumption of and access to fruit and vegetables	2,3,4	2,3,4	2,3	2,3,4	2,3,4
Decrease consumption of high fat, sugar, salt and energy dense foods	2,3	1,2,3	2,3	1,2,3	1,2,3
Increase water consumption	1,2,3,4	1,2,3,4		1,2,3,4,5	1,2,3,4
Decrease consumption of high sugar drinks	1,2,3,4	1,2,3,4		1,2,3,4	1,2,3,4
Increase the number of recreational opportunities for students/adults	3,4,5		2,3	3,5	5
Increase opportunities for formal and/or informal physical activity	2,3,4	2,3	2,3	2,3,4	2,3,4
Increase active transport		3		3,5	1,2
Increase awareness of healthy eating and physical activity guidelines	4,5			1,2,4	1,2,3,5
Increase initiation and duration of breastfeeding				2	
Improve healthy lifestyle using intergenerational and role modeling approaches	1		1	1,2	1,2
Foster positive body image	3			3	3
Community capacity building (leadership, partnerships, infrastructure etc)	1,2,3,4,5	2	1,5		

*The numbers relate to the specific intervention communities (1-5), see table 1 for more details.

A logic model was also developed on the basis of the action plans and frameworks being utilized to guide the intervention activities (see Figure 1). This logic model extended comparable models developed for other similar community-based projects, and provides a practical method for systematically collecting evaluation data for community projects [14].

**Figure 1 F1:**
[figure not shown]
**Program logic model of the Health Promoting Communities: Being Active Eating Well initiative**.

### Evaluation design

The evaluation design will be quasi-experimental, repeat cross-sectional, with outcomes compared between intervention and comparison areas at two time points within the project duration (2008/9 and 2010). The socio-ecological model of health has been utilized to develop the intervention activities and evaluation design. This framework focuses attention on five key determinants of health behavior: individual factors, interpersonal and primary groups; institutional and organizational factors, community factors and public policy [15]. The model assumes that appropriate changes in the social environment will produce changes in individuals and the support of individuals in the population is essential for implementing environmental changes [16]. Consistent with this framework, impact and outcome data will be collected at the community, setting and individual levels. Table 3 provides an overview of the evaluation data to be collected.

**Table 3 T3:** Overview of the multi-level and mixed methods evaluation data to be collected

Level	Details	Tools
**Community**	Networks and partnerships Opportunities for physical activity Access to nutritious food Policy development and implementation Capacity building	Partnership/community assessment Document analysis Key informant interviews (post intervention)
**Workplace**	Environment Access to healthy food Opportunities for physical activity Policy development	Environment assessment Document analyses
**School**	Socio-cultural environment Policy development and implementation Capacity building Access to nutritious food Opportunities for physical activity	School environment assessment
**Individual**	Food and activity related behaviors Weight status Quality of life	Health behavior questionnaire Anthropometric Assessment Quality of Life Questionnaire

### Comparison groups

Appropriate comparison groups for each target (age) group will be selected from across the state. Comparison schools will be randomly drawn from Victorian schools matched on demographics including school type (government/non-government), school size, level of disadvantage (using the Socio-Economic Index for Areas [SEIFA] index of advantage/disadvantage Victorian decile from the 2006 Census [17]) and location (Local Government Area and region). Comparison workplaces will be matched on the demographic characteristics of the intervention workplaces, including the workplace size, type and location.

### Sample size

The sample size calculations were primarily designed to account for intervention outcomes and detect a meaningful level of change compared to the comparison group. As such, calculations were based on a difference in behavior prevalence of > 15% and zBMI > 0.15 units between intervention and comparison groups, while also accounting for the design effects of clustering by schools and workplaces. Detecting differences within this design will require a sample of approximately 5,200 students (approximately 2,400 primary students and 2,800 secondary students). For the adult sample, 245 people in the intervention and a matched comparison sample will have the power to detect a 13 percentage point difference in behavioral outcomes (power of 80%) and difference of 1.7 BMI units between intervention and comparison samples with 80% power at a significance level of 0.05.

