### Impact and outcome evaluation

Differences in individual and community-level impacts and outcomes will be measured using a cross-sectional design with differences between intervention and comparison groups assessed at the cluster (school, workplace, community) level as appropriate. Trained research staff (supported by project staff at baseline) will collect the anthropometric, behavioral, quality of life and environmental data from each school/workplace pre- (2008/9) and post- (2010) intervention activities. Data on socio-demographics will also be collected in two ways: direct data collection from the participant (age, gender, country of origin, residential address, school address) and from the community (region) using the 2006 ABS Census data (e.g. mean income, education, occupation, indigenous status, family structure, country of origin, English-speaking). This community level data will be used in hierarchical linear modeling to analyze the outcomes of the interventions. At the local level, additional intervention impacts will be captured through qualitative methods (narrative evaluation, case studies, photo diaries etc).

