### Data entry, handling and statistical analysis

The child behavioral surveys will be scanned directly into an electronic database. The demographic, other survey (adult behavioral and AQoL) and anthropometric data will be double-entered into Stata (Version 10.1, StataCorp, College Station, Texas, USA). All statistical analysis on individual and school environment data will be conducted using Stata and quantitative analysis of the cross-sectional impact and outcome data will utilize regression analysis, hierarchical linear modeling, descriptive statistics and design corrected chi^2 ^analysis, as appropriate. The SVY commands in stata will be used for all analysis to account for clustering and design effects and the primary analysis will be between the intervention and comparison groups post-intervention. Demographic data will be used to adjust for confounding (e.g. gender; socio-economic status), and additional data on smoking status and alcohol intake will be collected from adults. Qualitative data will be analyzed using content and inductive thematic methods, as appropriate. Data triangulation and mixed methods analysis will also be used where possible.

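### The sample size allows for clustering by school and workplace only, although the intervention is applied to one or two whole communities per target group, so the stated detectable differences and adult power assume zero between-community variance.

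*Protocol article*

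**What the plan says.** The Background section of the protocol article says: "The intervention will operate at a whole-of-community level within five intervention sites". Table 1 (Intervention communities) names communities 1 and 2 for primary-school-age children, 3 and 4 for secondary students, and 5 for working adults.

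The Sample size section uses a "difference in behavior prevalence of > 15% and zBMI > 0.15 units" for students, "while also accounting for the design effects of clustering by schools and workplaces". It asks for "approximately 2,400 primary students and 2,800 secondary students". For adults it takes 245 in the intervention sample and a matched comparison sample. It states 80% power for 13 percentage points in behaviour, and for 1.7 BMI units "with 80% power at a significance level of 0.05". It gives no ICC, cluster size, design effect or SD.

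On analysis, Impact and outcome evaluation lists school, workplace and community as possible cluster levels, to be used as appropriate. Of area census data it adds: "This community level data will be used in hierarchical linear modeling to analyze the outcomes of the interventions". Data entry, handling and statistical analysis says: "The SVY commands in stata will be used for all analysis to account for clustering and design effects". It does not say which unit the survey commands will treat as the cluster. The primary contrast is between groups after the intervention.

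**The concern.** Exposure varies between communities, not between schools within a community. Schools in one intervention community share the same programme and the same local conditions and trends. They are therefore not independent replicates of the intervention. Recruiting more students or schools inside the same two communities does nothing to reduce the variance between communities.

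The sample-size basis stops one level below the level of exposure. The primary contrast is post-intervention and assignment is not random, so existing differences between communities stay in the contrast except where matching or covariates remove them. With one adult intervention community, the community and the intervention cannot be separated within that arm.

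At stake is whether ordinary differences between communities could be reported as effects of the initiative. This matters because the abstract expects the results to "guide the development and implementation of future obesity prevention efforts in Australia and internationally", which looks beyond the five communities studied.

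**Working it through.** **Reproducing the stated figures (two-sided 0.05, 80% power, 1.960 + 0.842 = 2.80).**

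- Students, 0.15 zBMI, SD 1 assumed: n per group = 2 × 2.80² × 1² / 0.15² ≈ 698, or 1,396 in total without clustering. The planned 2,400 and 2,800 then imply design effects of 2,400/1,396 = 1.72 and 2,800/1,396 = 2.01.
- Adults, 1.7 BMI units: 245 per group gives 80% power at SD 6.7 with no design effect. At SD 5, 136 per group suffice, which implies 245/136 = 1.80.
- Adults, 13 points: at base prevalences of 37% to 50%, 228 to 232 per group are needed, or 243 to 247 with continuity correction. The latter matches 245 with no clustering allowance. At a base of 20% the need is 180, implying 1.36.

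Reproduction is thus conditional on inputs the article does not state. For scale, with a 1:1 split there are about 600 primary or 700 secondary students per intervention community. At community ICC 0.005, 1 + (m − 1) × ICC is 4.0 or 4.5, well above 1.7 to 2.0.

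**Adding between-community variance.** I took the SE that gives exactly 80% power for the stated difference as the school- or workplace-level SE, so the plan's own clustering allowance is granted in full. I then added the intervention-arm term and treated comparison areas as widely dispersed.

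- Students by age group (two communities): SE0 = 0.15/2.80 = 0.0535; SE = √(SE0² + ICC/2).
- Students pooled (four communities, same SE0): SE = √(SE0² + ICC/4).
- Adult BMI (one community, SD 5 assumed): SE0 = 1.7/2.80 = 0.607; SE = √(SE0² + 25 × ICC).
- Adult behaviour (variance 0.25 assumed): SE0 = 0.13/2.80 = 0.0464; SE = √(SE0² + 0.25 × ICC).
- Detectable difference = 2.80 × SE; power = Φ(Δ/SE − 1.96); type I error if community is ignored = 2 × [1 − Φ(1.96 × SE0/SE)].

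| Community ICC (assumed) | Students by age group: detectable zBMI; type I | Students pooled: detectable zBMI; type I | Adult BMI: power; type I | Adult 13 points: power; type I |
|---|---|---|---|---|
| 0 | 0.15; 5% | 0.15; 5% | 80%; 5% | 80%; 5% |
| 0.002 | 0.174; 9% | 0.163; 7% | 75%; 7% | 71%; 8% |
| 0.005 | 0.205; 15% | 0.180; 10% | 68%; 9% | 61%; 12% |
| 0.01 | 0.248; 24% | 0.205; 15% | 58%; 13% | 48%; 18% |

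Example, students by age group at ICC 0.01: √(0.0535² + 0.005) = 0.0887, and 2.80 × 0.0887 = 0.248.

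Three qualifications apply:

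- Dispersed comparison areas are the favourable case. If comparison schools also came from two areas, the student range by age group would be 0.195 to 0.318.
- The pooled column assumes 0.15 is the target for the pooled sample. If each age group alone reaches 0.15, pooling halves both variance terms. The SE ratio, and so the 9% to 24%, is then the same as by age group.
- Normal quantiles ignore the few degrees of freedom. A two-versus-two community t test (2 df) has about 35% power at ICC 0.

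**The case against.** The strongest reply is that the analysis is not fixed at school or workplace level. Impact and outcome evaluation names community as a cluster level, hierarchical models are planned, and a condensed article may leave the cluster unit to a fuller document. This stands for the analysis. A reader might infer that the plan leaves community variance out of its standard errors, but the article does not say so. Understated standard errors are a risk from unsettled text. The reply does not rescue the Sample size section, which names its cluster levels and omits community. Nor do community covariates in a hierarchical model by themselves supply a community error term.

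The abstract also plans a combined analysis across the projects, so counting communities by age group may be too severe. This stands in part, and the pooled figures are shown for that reason.

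Matching on disadvantage and location (Comparison groups) and covariate adjustment may shrink residual community variance. That is fair. It argues for the lower end of the ICC range, not for zero.

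Two further readings are tempting and fail:

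- One might say that the census covariates are too many for one or two intervention communities. Comparison areas across the state also inform those coefficients, and the census items are given as examples, not as a fixed model.
- One might say that no error term can exist for adults. Comparison areas can supply one if between-community variance is assumed equal in both arms.

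**Conclusion.** The point holds for the sample size and, as a risk, for the analysis. The stated detectable differences and the adult 80% power require zero between-community variance, which the article neither states nor supports.

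At community ICCs of 0.002 to 0.01, the student detectable difference is 0.17 to 0.25 zBMI by age group or 0.16 to 0.21 pooled, against 0.15. Adult power is 75% to 58% for BMI and 71% to 48% for behaviour, against 80%. The type I error figures apply only if community is ignored in the analysis.

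The sizes rest on assumptions: the ICC range, SD 1 for zBMI, SD 5 for BMI, variance 0.25 for behaviour, a 1:1 split, dispersed comparison areas, and 80% power for students. The article states power for adults only, so a shortfall from a stated student power cannot be claimed. The direction does not depend on these values: any positive community variance makes the stated figures too favourable.

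**What to change.** 1. In Sample size, restate the detectable differences and adult power as conditional on no between-community variance, and give a range over assumed community ICCs.
2. For individual outcomes, fit a hierarchical model with a community (Local Government Area) random intercept above school or workplace. Estimate it across intervention and comparison areas, with small-sample degrees of freedom. Otherwise, state that inference is conditional on these communities. Reconcile the wording of the sample-size and analysis sections on the cluster unit.
3. Report the adult result as a single-community comparison, and say that any between-community error term is borrowed from comparison areas under a common-variance assumption.

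Do not simply declare community the primary sampling unit under the survey commands. With one or two such units in an arm, the linearised variance is unreliable. Null simulations of an adult-type layout (one intervention community with eight clusters, eight comparison communities with one each, cluster ICC 0.01, community ICC 0.002 to 0.01) gave type I error of 17% to 25% with community as the unit against 8% to 16% with the school or workplace. With larger clusters the figures were 19% to 30% against 9% to 21%.

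The planned community covariates need no change on this account. The cost is wording and model specification, wider intervals and less favourable stated figures. No extra participants are needed.

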### Process evaluation

The primary methods to assess the extent to which the intervention activities have been implemented and determine program reach (process evaluation) will include: document analysis (e.g. meeting minutes, action plan versions, reports, school/workplace policies, food service menus, and curriculum); key informant interviews; participant feedback; focus groups; case studies of participants/community organizations and surveys. At a local level, project managers and workers will also capture the approaches to intervention development and promotion, participant recruitment, level of (and explanation for) participation and non-participation, demographics of participants (e.g. gender, socio-economic position, age group) and any publicity or press for the local project. Together this data will comprise the process evaluation.

